### Eligibility criteria

Inclusion and exclusion criteria were set following the recommendations made by the authors of the UP [27] (Table 1).

**Table 1 Tab1:** Eligibility criteria

Inclusion criteria	
1	Anxiety disorder, mood disorder, or adjustment disorder is the main diagnosis (most interfering and severe)^a^
2	The patient is over 18 years of age
3	The patient is fluent in the language in which therapy is performed (Spanish in the present study)
4	The patient is able to attend to the evaluation and treatment sessions and signs the informed consent form
5	Patients taking pharmacological treatment for their emotional disorder are asked to maintain the same dosages and medications for at least 3 months prior to enrolling in the study and during the whole treatment^b^
Exclusion criteria	
1	The patient presents a severe condition that would require to be prioritized for treatment, so that an interaction between both interventions cannot be ruled out. These include a severe mental disorder (bipolar disorder, schizophrenia, or an organic mental disorder),suicide risk at the time of assessment, or substance use in the last three months (excluding cannabis, coffee, and / or nicotine)
2	The patient has previously received 8 or more sessions of psychological treatment with clear and identifiable CBT principles within the past 5 years.

^a^The following disorders will be included based on DSM-IV-TR diagnostic criteria [21]: major depression disorder, dysthymic disorder, panic disorder, agoraphobia, obsessive-compulsive disorder, generalized anxiety disorder, posttraumatic stress disorder, social anxiety disorder, hypochondria, and adjustment disorders. Patients with unspecified anxiety disorders and unspecified depressive disorders will also be included as they are frequent in public settings

^b^If medication stability is not possible, the participant’s data will be treated separately in the analyses

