## Methods/design

The current study is a non-inferiority, multicenter, randomized, controlled clinical trial with two treatment groups: UP in group format and traditional CBT in individual format (treatment as usual, TAU). A conservative, non-inferiority design was selected because, to the best of our knowledge, this is the first randomized controlled trial to compare the UP in a group format against individual CBT in public mental health settings.

In the present investigation, all consecutive patients with EDs attending any of the collaborating centers (see “Sample and recruitment” section) are asked to participate. Once inclusion criteria are met (see “Inclusion and exclusion criteria” section), each patient is randomly assigned to one of the two experimental groups: TAU or UP (see “Procedure” section). The study includes 5 assessment points (baseline, post-treatment, and three follow-ups at 3, 6, and 12 months after treatment completion). The flow chart of study design is shown in Fig. 1. Also, a schedule of enrolment, interventions, and assessments is reported following the Standard Protocol Items: Recommendations for Interventional Trials (SPIRIT) guidelines (Fig. 2). Note that, despite treatment occurs at different frequencies between conditions (approximately once a month in the TAU condition and weekly in the UP group), assessment points are the same for both groups.

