### Treatment as usual (TAU)

Individual CBT is the treatment of choice by psychologists and psychiatrists at the collaborating Public Mental Health Centers and Primary Care Centers, together with pharmacological treatment (i.e., antidepressants and / or anxiolytics). Clinicians in this condition complete a self-report sheet describing the characteristics of their interventions with treatment modules as cues (psychoeducation module, identification of negative thoughts, breathing training, etc.), the average duration of sessions, number of sessions delivered, and end-of-treatment date, as well as information on the number of appointments with the psychiatrist and pharmacological treatment prescribed during the study. Information on the number of appointments with the psychiatrist and pharmacological treatment prescribed during the study is also collected for patients in the UP group following the same procedure described for the CBT condition.

As opposed to the UP condition, in which the duration of treatment is fixed (12 sessions), the usual practice in Spanish public settings is that treatment ends when both the clinician and the patient agree that the intervention has been effective. This is not necessarily guided by questionnaires or a diagnostic interview, but on clinical judgment. Because the study goal is to compare a new treatment (UP in a group format) with the usual practice in Spanish public settings, the same procedure described above will be used to determine the end of treatment in the TAU condition and no specific end points (i.e., a decrease in questionnaire scores) or number of sessions will be imposed. Because this is likely to yield different treatment durations between study conditions, the treatment duration (number of sessions) will be used as a covariate in the analyses.

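### A medication change after randomisation may put a patient outside the main comparison, which sits badly with the promised intention-to-treat analysis

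*Protocol article*

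**What the plan says.** Inclusion criterion 5 (Eligibility criteria, Table 1) states that patients who are on medication "are asked to maintain the same dosages and medications for at least 3 months prior to enrolling in the study and during the whole treatment". Footnote b gives the consequence where this cannot be kept up: the person's "data will be treated separately in the analyses". Both apply to either arm.

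The section on TAU describes individual CBT at the centres as given "together with pharmacological treatment (i.e., antidepressants and / or anxiolytics"). Clinicians record psychiatrist appointments and drugs prescribed during the study, and for the other arm too: "pharmacological treatment prescribed during the study is also collected for patients in the UP group".

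Treatment time differs by arm. Sessions run "approximately once a month in the TAU condition and weekly in the UP group" (Methods/design). UP is fixed at 12 weekly sessions, whereas in usual practice "treatment ends when both the clinician and the patient agree that the intervention has been effective", and TAU follows that practice with no set number of sessions.

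The Abstract and the Analyses section promise intention-to-treat and per-protocol analyses. The Analyses section limits the intention-to-treat strategy by session attendance and by having at least one post-treatment assessment. It does not mention medication.

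**The concern.** Footnote b makes the handling of a randomised patient's data depend on something that can happen after allocation. A change of drug or dose during treatment plausibly follows poor response, and its frequency may differ by arm. If such patients are analysed apart from the rest, the main comparison is made between groups selected on a possible consequence of treatment, and randomisation no longer protects it.

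Unequal loss is plausible because the period in which a change counts runs for the whole of treatment. That is 12 weeks in UP and open-ended, at roughly monthly sessions, in TAU, so slow responders in TAU may stay exposed to the rule for longer.

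Two things are at stake. One is bias in the difference on which non-inferiority is judged, in a direction that cannot be known in advance. The other is power, because the 110 per arm allows only for dropout.

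The part of the rule that concerns the three months before enrolment is a different matter. Separating patients on a pre-randomisation characteristic does not break the randomised comparison, and this point does not extend to it.

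**Working it through.** **1. Inputs from the protocol article (Sample size).** Margin .30, SD .83, one-sided alpha .05, power 80%, 95 per arm, 15% dropout, 110 recruited per arm.

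**2. The plan's own figure.** With a true difference of 0, n per arm = 2 × .83² × (1.645 + .842)² / .30² = 94.6, which rounds up to 95. The stated figure is reproduced. For dropout, 95/(1 − .15) = 111.8, or 112, and 95 × 1.15 = 109.3, or 110; the stated 110 is within two patients of 112. After 15% dropout, 110 × .85 = 93.5 per arm remain, with power Φ(.30/(.83 × √(2/93.5)) − 1.645) = 79.6%. Nothing is set aside for medication changes.

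**3. Inputs the article does not give.** The share of each arm with a medication change, and how much worse those patients do. I assume shares of 10% to 30% and a gap of .25 to .8 SD, the same in both arms, with .5 SD (.5 × .83 = .415) as the middle case. I also assume that changers would be removed from the main comparison and that dropout is unrelated to medication change.

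**4. Formulas.** The difference is UP minus TAU, higher being worse.
- n in each arm = 93.5 × (1 − share removed)
- Shift = (share removed in TAU − share removed in UP) × gap
- SE = .83 × √(1/n_TAU + 1/n_UP)
- Power at a true difference of 0 = Φ((.30 − shift)/SE − 1.645)
- One-sided type I error at a true difference of .30 = Φ(−1.645 − shift/SE)

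**5. Results with a gap of .415.**

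| Removed TAU / UP | n TAU / UP | Shift | Shift as share of margin | Power | Type I error |
|---|---|---|---|---|---|
| 0 / 0 | 93.5 / 93.5 | 0 | 0 | 79.6% | 5% |
| 20% / 20% | 74.8 / 74.8 | 0 | 0 | 71.4% | 5% |
| 20% / 10% | 74.8 / 84.2 | +.042 | 14% | 62% | 2.5% |
| 25% / 10% | 70.1 / 84.2 | +.062 | 21% | 55% | 1.7% |
| 30% / 10% | 65.5 / 84.2 | +.083 | 28% | 48% | 1.2% |
| 10% / 30% | 84.2 / 65.5 | −.083 | 28% | 88% | 15% |

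Worked example, 25% / 10%: shift = (.25 − .10) × .415 = .062, and .062/.30 = 21%. Worked example, 10% / 30%: SE = .83 × √(1/84.15 + 1/65.45) = .137, and type I error = Φ(−1.645 + .083/.137) = 15%.

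**6. Range.** In the 10% / 30% case, gaps of .25 to .8 SD give a type I error of 9% to 25%. In the 30% / 10% case they give a shift of .04 to .13 against UP. With equal shares and equal gaps the shift is zero and only power is lost.

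**The case against.** The strongest reply is that the article never says these patients are excluded. Treating data separately could mean a subgroup, sensitivity or per-protocol analysis, and a per-protocol analysis is already planned. Medication is not among the restrictions on the intention-to-treat strategy, and the details may lie in an analysis plan that is not shown. This stands as far as it goes: removal is an inference from the footnote. But the footnote is the only rule the article gives for these patients. Its plain sense is analysis apart from the others, and it is not tied to a secondary analysis. Left open, membership of the main comparison could be settled after the data are seen.

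A reader might also infer that TAU contains drug treatment by definition and will therefore lose more patients. The documents do not support that. The two arms are defined by therapy and format, drug treatment is described as part of usual practice, prescribing is recorded in UP as well, and the rule covers both arms. The longer, open-ended TAU course makes unequal change plausible and no more.

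A reader might further infer that criterion 5 contradicts the TAU description. It does not: a patient can have CBT alongside a drug regimen and be asked to keep that regimen unchanged. The passages are in tension, because the article does not say how drugs newly prescribed during treatment relate to the stability request.

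Finally, if TAU does lose more poor responders, the retained TAU group looks better and the bias runs against UP, which is conservative for a non-inferiority claim. That is correct. The opposite pattern is the one that favours a false claim, and the article neither rules it out nor gives a reason to expect it.

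**Conclusion.** The point holds in a limited form. Footnote b combined with criterion 5 allows a randomised patient in either arm to be analysed apart from the main comparison because of a post-randomisation event. On its natural reading this conflicts with the intention-to-treat commitment. The stronger statement, that such patients are removed and the arms lose them selectively, goes beyond the text.

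The size cannot be established from the article, because every share and gap above is assumed. In the middle cases a shift of about 14% to 28% of the margin is possible in either direction. It costs power when TAU loses more and inflates the type I error when UP loses more. The loss of power under equal removal needs no assumption about bias, only that patients are taken out. The matter should be corrected, but it does not by itself invalidate the design.

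**What to change.** State in the Analyses section that all randomised patients stay in the primary analysis whatever happens to their medication after randomisation. Report medication changes by arm. Use the medication-stable set only as a sensitivity or per-protocol analysis, and reword footnote b to say so. The authors should reconcile footnote b with the intention-to-treat statement and make clear how criterion 5 fits with the TAU description, including whether a drug started during treatment triggers the footnote. This is a matter of the authors' own text; no clinical rule is proposed here.

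The cost is wording only. Prescribing during the study is already recorded in both arms, so no further data collection or recruitment is needed.

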### Ethics

This study is carried out in accordance with the study protocol, the Helsinki Declaration, and good clinical practice. This non-inferiority, multicenter, randomized, controlled clinical trial has been approved by ethical and research committees of all collaborating centers: Hospital General Clínico de Elda (N°. PUG-02-14), Hospital Clínico Universitario de Valencia (N°. F-CE-GEva-15), Hospital Universitario [name] (N°. CEIC 53/15), CSM IIA Milagrosa (N°. Pyto2016/41), and Hospital Comarcal de Vinaròs (N°. 0103–2016). Data handling is carried out according to premises established by Spanish laws [28]. Security and confidentiality of participants’ data are guaranteed by using alphanumeric codes (SUP001) instead of names.

### Therapists and interventions

Therapists participating in the study include licensed psychologists with between 8 and 20 years of experience in delivering CBT, clinical psychology residents with 2 to 4 years of experience, and doctoral students in clinical psychology with between 3 and 5 years of experience.

### Unified protocol in group format

Our research team has adapted the UP [8, 9] to implement it in group format in a public mental health setting in Spain. This adaptation is composed of 12, two-hour treatment sessions, at a rate of one session per week. Treatment content, split by session, is shown in Table 2.To encourage maximum fidelity to the protocol, all therapists participating in this condition received a UP training course prior to study onset, as well as videoconference supervision before every session. The course consisted of a 20-h group workshop divided in 3 sessions. Next, all therapists received an individual training during 12 therapy sessions. Depending on availability, this individual training consisted of an online supervision before sessions or it involved acting as a co-therapist. Supervision is conducted by the leading author, [name], who has been certified UP Researcher/Trainer by the Unified Protocol Institute.

**Table 2 Tab2:** Treatment content split by session

Session number	Content
Session1	Motivation for change and commitment to treatment
Session2	Understanding the adaptability of emotions
Session3	Recognition and analysis of emotions
Session4	Emotional awareness training - I
Session5	Emotional awareness training - II
Session6	Cognitive flexibility- I
Session7	Cognitive flexibility- II
Session8	Emotional avoidance and emotion-driven behaviors
Session9	Consciousness and tolerance to physical sensations
Session10	Interoceptive and situational emotional exposure- I
Session11	Interoceptive and situational emotional exposure- II
Session12	Achievements, maintenance, and relapse prevention

Participants who miss one or more UP sessions receive a phone call from the group therapist to explore the reasons for non-attendance, as well as to encourage reading the materials that summarize missed sessions. Also, at the beginning of each session the therapist reviews important contents of the past session to minimize this effect of missed sessions.

### Treatment as usual (TAU)

Individual CBT is the treatment of choice by psychologists and psychiatrists at the collaborating Public Mental Health Centers and Primary Care Centers, together with pharmacological treatment (i.e., antidepressants and / or anxiolytics). Clinicians in this condition complete a self-report sheet describing the characteristics of their interventions with treatment modules as cues (psychoeducation module, identification of negative thoughts, breathing training, etc.), the average duration of sessions, number of sessions delivered, and end-of-treatment date, as well as information on the number of appointments with the psychiatrist and pharmacological treatment prescribed during the study. Information on the number of appointments with the psychiatrist and pharmacological treatment prescribed during the study is also collected for patients in the UP group following the same procedure described for the CBT condition.

As opposed to the UP condition, in which the duration of treatment is fixed (12 sessions), the usual practice in Spanish public settings is that treatment ends when both the clinician and the patient agree that the intervention has been effective. This is not necessarily guided by questionnaires or a diagnostic interview, but on clinical judgment. Because the study goal is to compare a new treatment (UP in a group format) with the usual practice in Spanish public settings, the same procedure described above will be used to determine the end of treatment in the TAU condition and no specific end points (i.e., a decrease in questionnaire scores) or number of sessions will be imposed. Because this is likely to yield different treatment durations between study conditions, the treatment duration (number of sessions) will be used as a covariate in the analyses.

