### Analyses

First, we will calculate between-group differences in baseline measures, to ensure that randomization resulted in comparable groups. When normally distributed, continuous data will be analyzed via *t* test. If the Kolmogorov-Smirnov test indicates a non-normal distribution, a Mann-Whitney *U* test will be preferred. A chi-square test will be performed for categorical data. Then, to compare the efficacy of treatments, we will use a mixed-effects regression modeling with full information maximum likely hood estimation. This method is recommended over repeated-measures ANOVAs due to its flexibility in handling missing data [39]. Group (TAU or UP) will be used as the between-subject factor and time (baseline, post-treatment, and follow-ups) as the within-subject factor. Standardized effect sizes (Cohen’s *d*) will be calculated both for within and between-group analyses. Covariates will be demographic and clinical variables that are not comparable between groups, as exposed in the beginning of this section. Effect estimators in the UP group will be adjusted to control for the impact of group dependencies (i.e., homogenization of response to treatment due to shared environment), following the recommendations of Baldwin et al. [40].

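### Number of sessions, set after randomisation and differently in each arm, is fixed as a covariate; the adjusted contrast is not the stated comparison, and its bias has unknown size and sign

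*Protocol article*

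**What the plan says.** The commitment is in the Treatment as usual (TAU) section. Because durations are expected to differ between arms, "the treatment duration (number of sessions) will be used as a covariate in the analyses". No model is named, and the adjustment is not labelled primary, supportive or exploratory.

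The same section says how the covariate comes about. UP is fixed at 12 sessions. In usual practice, "treatment ends when both the clinician and the patient agree that the intervention has been effective"; the trial keeps that rule, so "no specific end points (i.e., a decrease in questionnaire scores) or number of sessions will be imposed". It also gives the reason for leaving TAU alone: "the study goal is to compare a new treatment (UP in a group format) with the usual practice in Spanish public settings".

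Two other places bear on this. Methods/design gives the session frequency as "approximately once a month in the TAU condition and weekly in the UP group", with assessments placed relative to treatment completion. The Analyses section describes the mixed model and gives a different covariate rule: "Covariates will be demographic and clinical variables that are not comparable between groups", as identified by the baseline comparison. It does not mention session count.

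**The concern.** A covariate measured before randomisation cannot be changed by the assigned treatment. Session count can. In UP it is set by the arm; in TAU it is at least partly set by how the patient is doing. Conditioning on it replaces the randomised comparison with one between UP patients and a model projection of TAU patients to a similar number of sessions.

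Three things in the document make this a wrong choice and not a matter of taste.

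- The length of TAU as it naturally occurs is part of the comparator the authors want. Adjusting it away answers another question.
- Equal session counts do not mean equal time. Twelve weekly sessions take about 12 weeks; twelve monthly sessions take about 12 months.
- The covariate is outside the rule in the Analyses section, so the document gives two covariate sets for what reads as the same analysis.

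What is at stake is the non-inferiority conclusion. The confidence bound for the UP-TAU contrast is compared with a margin of .30, so a shift of a few tenths can decide the result either way.

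**Working it through.** **Inputs from the document.** Margin .30, SD .83, one-sided alpha .05, 80% power, 95 per group (Sample size section); 12 sessions in UP and no imposed number in TAU (Treatment as usual section).

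**Inputs that are assumptions.** TAU session mean *m* and SD *s*; correlation *rho* between sessions and post-treatment score within TAU; attendance in UP (normal, mean 11, SD 1.5, capped at 12, which gives a realised mean of about 10.8 and SD of about 1.2); no session-outcome relation within UP. The document gives none of these.

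**Step 1: the plan's own figure.** n = 2 × (1.645 + 0.842)² × 0.83² / 0.30² = 94.6, so 95 per group. The stated size reproduces, with 80% power when session count is not in the model.

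**Step 2: formula for the shift.** Take the contrast as UP minus TAU, with higher scores worse, so a negative shift favours UP. In a linear model with arm and sessions, the adjusted contrast differs from the unadjusted one by

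shift = -(rho × SD / s) × [s² / (s² + s_U²)] × (m_U - m),

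where m_U and s_U are the mean and SD of sessions in UP. If every UP patient is entered as 12, the bracket is 1 and the shift is -rho × SD × (12 - m) / s.

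**Step 3: numbers.** With s = 3, rho = +0.3 and s_U = 1.2: 0.3 × 0.83 / 3 = 0.083; 9 / (9 + 1.44) = 0.862; product 0.0716. Multiplying by (10.8 - m) gives the second column. Simulation of the linear model with 95 per arm gives the other two.

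| TAU mean sessions | Shift, formula | Shift, simulated | Type I error at a true difference of .30 (nominal 5%) |
|---|---|---|---|
| 6 | -0.34 | about -0.35 | about 65% |
| 8 | -0.20 | about -0.20 | about 43% |
| 10 | -0.06 | about -0.05 | about 12% |
| 12 | +0.09 | about +0.08 | about 1% |

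With rho = -0.3 the shifts have the same size and the opposite sign. With rho = 0 they vanish.

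**Step 4: loss of precision without bias.** The variance of the contrast is inflated by 1 + (m_U - m)² / [2(s² + s_U²)]. At m = 6 this is 1 + 4.8² / 20.88 = 2.1; at m = 8 it is 1 + 2.8² / 20.88 = 1.4. The unadjusted standard error is 0.83 × √(2/95) = 0.120. At m = 6 it becomes 0.120 × √2.1 = 0.174, and power is Φ(0.30/0.174 - 1.645), about 53%. At m = 8 it becomes 0.120 × √1.4 = 0.142, and power is about 68%. Simulation gives about 51% and 69%, against 80% unadjusted. At means of 10 to 12 there is little loss.

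**Step 5: limiting case and scale.** With UP entered as exactly 12, m = 6 and s = 3, the shift at rho = +0.3 is -0.3 × 0.83 × 6/3 = -0.50; at m = 12 it is zero. The document does not say whether the .30 and the .83 are on the same scale. If the SD is 1, the formula shifts are larger by 1/0.83: about -0.41 at mean 6 and -0.24 at mean 8.

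**The case against.** The strongest reply is that the size is borrowed. A reader might infer that the adjustment biases the contrast by more than the margin. The document does not support that: it gives no expected TAU session count, spread or correlation with outcome. In the table only a TAU mean of 6 passes .30; at 8 and 10 the shift is smaller, and at 12 it changes sign. Since no number of sessions is imposed in TAU, a mean of 12 is as open as a mean of 6. This part of the objection stands.

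A reader might also infer that session count is almost collinear with arm. It is not under these assumptions: the variance inflation is a little over 2 at a TAU mean of 6, about 1.4 at 8, and close to 1 at 10 to 12. The article also expects some missed UP sessions, so the count as attended would vary there too.

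Nor does the text fix the sign of the correlation. TAU ends on clinical judgement and not necessarily on questionnaire scores. If patients leave once they reach a similar level, scores may hardly depend on session count; if slower responders stay longer, more sessions go with worse scores.

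Finally, the Analyses section does not list the covariate, so the authors may have meant a supportive analysis. The article does not say so, and the wording in the TAU section is unqualified. The objection limits what can be claimed about size and direction. It does not rescue the choice of covariate.

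**Conclusion.** The point holds as a wrong analysis choice. The protocol commits to adjusting for a variable that is determined after randomisation, fixed by design in one arm and dependent on judged effectiveness in the other. The adjusted contrast does not estimate UP against usual practice as delivered, which is the goal given in the same section. Nor does the adjustment equalise elapsed time or agree with the covariate rule in the Analyses section.

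The size and direction of the bias are unknown. Across the assumed TAU means of 6 to 12 and a correlation of +0.3, the shift runs from about -0.35 to +0.08 and the type I error from about 65% to 1%; a negative correlation reverses the signs. With zero correlation the only cost is power, and only when TAU session counts are well below 12. These figures rest on a single linear slope and on the stated assumptions. They show that the conclusion could turn on the covariate, not that it will.

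**What to change.** Remove number of sessions from the primary model and from every non-inferiority model, both intention-to-treat and per-protocol, and use baseline covariates only. Reword the sentence in the Treatment as usual section so that it agrees with the covariate rule in the Analyses section. Report session count and treatment duration descriptively by arm. If a session-adjusted model is still wanted, show it only as a labelled exploratory analysis.

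The cost is a change of wording; no new data are needed. The downside is that the primary analysis no longer adjusts for treatment dose, which is consistent with the stated goal.

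An analysis by elapsed time since randomisation is optional and exploratory, not part of this fix. Assessments follow treatment completion, so the timing of TAU outcomes would itself depend on response, and there may be none near the UP post-treatment visit. The article also lists an end-of-treatment date only on the TAU clinicians' sheet.
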